### 2.8. Variables and Measures

#### 2.8.1. Main Dependent Variables

Feasibility will be assessed using automated metrics recorded by the platform, including the number of tasks completed, cognitive errors (omissions, commissions, impulsivity, sequencing, and monitoring), average session duration, and active usage rate. These indicators will be calculated based on the frequency of weekly participation [43,53]. Acceptability of the DiverAcción platform will be assessed using an adapted version of the Technology Acceptance Model (TAM). The questionnaire consists of 20 items grouped into six dimensions: Perceived ease of use (F), Perceived fun (DP), Intention to use (IU), Compatibility (C), Self-efficacy (AE) and Attitude towards use (AC). Each item is rated on a 5-point Likert scale (1 = strongly disagree, 5 = strongly agree), allowing for quantitative evaluation of user perceptions regarding usability, enjoyment, behavioral intention, and integration into daily routines. This adaptation ensures ecological validity by incorporating motivational and contextual factors relevant to telerehabilitation for ADHD. The TAM framework has been widely validated for predicting technology adoption and is considered a robust measure of acceptability in digital health interventions [54].Usability: Usability was evaluated using the System Usability The System Usability Scale (SUS) is a widely used standardized questionnaire for measuring the overall perception of the ease of use of systems and applications [55]. The SUS consists of 10 items that alternate between positive and negative statements, scored on a 5-point Likert scale (1 = “strongly disagree” to 5 = “strongly agree”). Responses are converted into a total score ranging from 0 to 100, where scores of 68 or higher are considered indicative of good usability. This instrument has demonstrated high reliability (α > 0.90) and validity in various contexts, making it a robust tool for evaluating user experience in digital environments.

#### 2.8.2. Secondary Dependent Variables

User-friendly design. The perception of the system’s ease of use and appeal will be assessed using a visual analog scale from 1 to 10, where 1 indicates an unfriendly experience and 10 reflects a highly intuitive and appealing design. This measure will allow for a quick and comprehensive evaluation of the perceived usability by participants, complementing other user experience indicators. The simplicity of this scale will facilitate its application in digital environments and its interpretation in terms of satisfaction and accessibility [54].Participant satisfaction. Satisfaction will be assessed using the Participant Satisfaction Questionnaire, consisting of 8 items in 4-point Likert format (1 = not at all satisfied; 4 = very satisfied), with a total score ranging from 8 to 32. Higher scores will reflect a greater level of satisfaction with the intervention.Therapeutic Alliance: The therapeutic alliance will be assessed using the Working Alliance Inventory for Internet Interventions (WAI-I) [27]. The WAI-I consists of 12 items rated on a 5-point Likert scale (1 = “never”, 5 = “always”), yielding a total score ranging from 12 to 60, with higher scores indicating a stronger alliance. The instrument evaluates three core components of the alliance—bond, goals, and tasks—and has demonstrated strong psychometric properties in digital health contexts, supporting its reliability for assessing collaborative engagement in online interventions.Therapeutic attitudes of professionals towards technology will be assessed using the e-Therapist Attitudes Toward Technology (e-TAP-T) [56]. This questionnaire will consist of 12 items using a 7-point Likert scale (1 = strongly disagree; 7 = strongly agree), designed to explore the professional’s level of commitment and willingness to use technological tools in clinical practice. The total score will range from 12 to 84, with higher scores indicating greater acceptance and commitment to technology. The e-TAP-T is considered a reliable measure for understanding attitudes that can influence the effective implementation of digital interventions.

#### 2.8.3. Effects Evaluation (Pre-Post)

The impact assessment of DiverAcción will be conducted using a multimodal approach that integrates different perspectives. Information will be collected focusing on children and adolescents, evaluating changes in planning, organizational, time management, and emotional self-regulation skills through standardized tests and objective metrics recorded by the platform. In parallel, questionnaires will be administered to parents and teachers to identify improvements in daily performance, and the transfer of strategies to natural contexts, as well as parental self-efficacy and stress. The opinions of therapists will also be considered, providing data on clinical applicability, program adherence, and the quality of the digital interaction. This approach will allow for a comprehensive view of the intervention’s effect, combining quantitative and qualitative indicators to ensure a robust and contextualized interpretation (Table 2).

Executive functioning will be assessed using the Behavior Rating Inventory of Executive Function, Second Edition (BRIEF-2) [57], in its parent and teacher forms. Both questionnaires employ a three-point Likert scale (Never, Sometimes, Often) to measure the frequency of behaviors associated with executive functioning in everyday contexts. The parent version will assess domains such as inhibition, emotional control, flexibility, working memory, planning and organization, and monitoring, while the teacher version will capture similar dimensions within the school setting. The combined application of the questionnaire will provide an ecological perspective, facilitating the identification of difficulties and the planning of tailored interventions. In addition, the adolescents themselves will complete a self-report on their executive functioning using the Teenage Executive Functioning Assessment (TEXI Inventory) [58]. The TEXI Inventory, comprised of self-report versions for adolescents and other-report versions for parents and teachers, aims to assess everyday executive functions such as working memory and inhibitory control. The questionnaire consists of 20 items distributed across two factors, and its administration follows standardized criteria in school and home settings. The psychometric robustness of the TEXI is supported by high internal reliability (α ≥ 0.85), split-form reliability (≥0.81), and strong inter-rater reliability between adolescent and parent reports (r = 0.82).Time management will be assessed using the Time-S questionnaire [59]. This instrument consists of items designed to measure the perception, organization, and control of time in daily and academic activities. It will be administered using a Likert scale, allowing for an overall score that reflects the level of competence in time management. Higher scores indicate a greater ability to plan, prioritize, and allocate time efficiently. The Time-S is considered an innovative and reliable tool for analyzing this dimension in educational and clinical contexts.The Emotion Regulation Questionnaire for Children and Adolescents (ERQ-CA) [60] will be administered to participating adolescents to assess their emotion regulation strategies in everyday life. The questionnaire will be administered digitally, after obtaining informed consent, in an environment supervised by the research team. Each participant will respond to the 10 items on a 5-point Likert scale (1 = “never” to 5 = “always”), obtaining independent scores for the two dimensions: Cognitive Reappraisal and Expressive Suppression. ERQ-CA scores are calculated by summing the scores for each subscale. Cognitive Reappraisal reflects the tendency to reinterpret situations to reduce their emotional impact; high scores indicate frequent use of adaptive strategies associated with better emotion regulation and fewer internalizing symptoms. Conversely, Expressive Suppression assesses the inhibition of emotional expression; high scores are associated with less affective expression and greater psychological distress. A balanced profile is characterized by high reappraisal and low suppression, while low scores in both dimensions may suggest difficulties in emotional regulation.Prospective and retrospective memory will be assessed using the Prospective and Retrospective Memory Questionnaire for Children (PRMQ-C) [61]. This self-report instrument employs a five-point Likert scale (1 = never; 5 = very often) to measure the frequency of everyday memory lapses in natural contexts. The questionnaire includes items targeting both prospective memory (remembering to carry out intended actions) and retrospective memory (recalling past information), allowing for a differentiated analysis of these components. Psychometric studies report adequate internal consistency (Cronbach’s α > 0.80) and good construct validity, supporting its use in both clinical and educational settings. The ecological nature of the PRMQ-C facilitates the identification of memory difficulties in daily life and supports the design of tailored interventions to enhance functional memory performance.The KIDSCREEN-52 is a standardized, self-report questionnaire created to evaluate health-related quality of life (HRQoL) in children and adolescents aged 8–18. It includes 52 items across 10 dimensions: physical well-being, psychological well-being, moods & emotions, self-perception, autonomy, parent relations & family life, financial resources, social support & peers, school environment, and social acceptance (bullying). Built on a multidimensional framework, it captures a comprehensive view of physical, emotional, and social well-being. Psychometrically, it shows high internal consistency (Cronbach’s α = 0.77–0.89 per subscale) and satisfies test–retest reliability, convergent and discriminant validity, as evidenced in a representative European sample (n ≈ 22,800). The instrument takes approximately 15–20 min to complete and is suitable for epidemiological surveys, clinical research, and evaluation of interventions targeting pediatric populations.The Brief Parental Self-Efficacy Scale (BPSES) [62], assesses parents’ perceptions of their parenting competence. The instrument consists of a reduced, 5-item version, tailored to a single construct of parental self-efficacy. Each item is answered using a 5-point Likert scale, generating a total score ranging from 5 to 25. The BPSES has demonstrated satisfactory psychometric properties: factor analysis confirmed a unidimensional solution (CFI = 0.96, RMSEA = 0.094), and the 5-item version achieved adequate internal reliability (α = 0.75).The Parenting Stress Index, Fourth The Parental Stress Index (PSI-4-SF) [63,64] will be used to assess parental stress levels throughout the study. This instrument is a widely validated measure that identifies the degree of strain experienced by caregivers in relation to the demands of the parental role. The PSI-4-SF consists of 36 items distributed across three subscales: Parental Stress, Dysfunctional Parent-Child Interaction, and Child Difficulty, each designed to capture different dimensions of stress within family dynamics. Responses are recorded on a 5-point Likert scale (from “strongly disagree” to “strongly agree”), generating scores that reflect both overall stress and stress specific to each subscale. Previous studies have reported excellent internal consistency for the abbreviated version, with Cronbach’s alpha coefficients greater than 0.90 at different assessment points (α = 0.91, 0.91, and 0.92), supporting its reliability and temporal stability.Time Management Scale for Teachers (EMT) [65]. The EMT is a questionnaire designed for teachers to assess their students’ time management in everyday school situations. It consists of 23 items using a Likert scale from 0 (never/rarely) to 3 (always/almost always), where higher scores indicate greater mastery of the time dimension. It has a two-factor structure: time used for tasks and time used for events. Internal consistency reliability is excellent: α = 0.95 for the total scale, α = 0.94 for Factor 1, and α = 0.90 for Factor 2. Higher scores indicate better time management.

#### 2.8.4. Independent Variables

Sociodemographic, educational and economic data (age, gender, educational level, school year, residence) and preferences regarding digital intervention format (online, face-to-face or hybrid), previous experience with digital interventions and ADHD symptomatology and associated behavioral difficulties, through SNAP-IV [66]. This instrument consists of 26 items rated on a 4-point Likert scale (0 = not at all, 3 = very much), covering three dimensions: Inattention (9 items), Hyperactivity/Impulsivity (9 items), and Oppositional Defiant Disorder (8 items). Higher scores indicate greater symptom severity. The SNAP-IV has demonstrated strong psychometric properties, including high internal consistency and validity for clinical and research settings [66].

### 2.9. Statistical Analysis

The statistical analysis plan was developed to reflect the primary aim of this feasibility study: to assess processes and practicality rather than confirm efficacy. Therefore, analyses will emphasize descriptive statistics and estimation of precision for feasibility metrics (e.g., recruitment, retention, adherence, fidelity, and data completeness), as recommended by CONSORT guidelines for pilot and feasibility trials [52,67]. Adherence thresholds (≥80% for agenda use and training, and 100% for videoconferences) were selected to ensure meaningful engagement with the online intervention. Fidelity procedures, including a 20-h therapist training course and structured supervision, aim to guarantee consistent delivery of the protocol. Missing data will be primarily described, with multiple imputation reserved for sensitivity analyses of exploratory outcomes, reflecting best practices for small-sample feasibility designs.

#### 2.9.1. Outcome Assessment and Bias Minimization

Outcome assessors will follow standardized administration and scoring procedures and will be blinded to intervention delivery, with no access to fidelity forms, session plans, or platform usage data. Self-report and performance-based measures will be administered through secure digital tools, with automated time stamps.

#### 2.9.2. Feasibility Outcomes

The primary aim of this study is to assess feasibility across multiple domains, following established frameworks for pilot and feasibility trials [52,67,68]. Progression criteria for feasibility outcomes are summarized in Table 3 and Figure 2.

The following outcomes will be evaluated:

*Recruitment and Retention*

Recruitment will be measured as the proportion of eligible participants who consent to participate, and the average recruitment rate per month. Retention will be defined as the percentage of participants who complete all planned assessments at T1 (post-intervention) and T2 (follow-up).

*Data Completeness and Missing Data*

Data completeness will be calculated as the proportion of participants providing valid data for each measure at each time point. Patterns and reasons for missing data will be documented. This information will inform the feasibility of data collection procedures and guide refinements for a future trial. Primary feasibility analyses will use complete cases. Sensitivity analyses using multiple imputation may be performed for exploratory clinical outcomes, but the results will be interpreted with caution given the small sample size.

*Adherence*

Adherence will be assessed based on three components:(a)use of the digital agenda on at least 80% of intervention days (over 6 weeks),(b)completion of at least 80% of scheduled online training activities, and(c)attendance at 100% of planned videoconference sessions.

Adherence will be reported as the proportion of participants meeting these criteria.

*Intervention Fidelity*

Fidelity will be ensured through a structured process: all occupational therapists delivering the intervention will complete a 20-h training course prior to implementation, covering theoretical foundations, intervention procedures, and use of digital tools. Fidelity will be monitored using session checklists, regular supervision meetings, and ongoing remote support. Fidelity will be categorized as high (≥80% of protocol elements delivered), moderate (60–79%), or low (<60%).

*Acceptability and Usability*

Acceptability will be explored through participant feedback collected via post-intervention questionnaires (TAM) [71], with a predefined threshold of mean ≥ 3.5 [70] and qualitative comments during videoconferences. Usability will be assessed using the System Usability Scale (SUS), considering scores ≥ 68 as acceptable [55]. Indicators will include perceived usefulness, ease of use, and satisfaction with the intervention format.

In the usability and acceptability evaluations, participants will have the opportunity to provide open-ended comments about their experience. These qualitative data will be recorded and analyzed using Atlas.ti 25 (25.0.2) software, following an inductive thematic analysis approach. Findings will inform iterative refinement of the intervention interface, task structure, and support strategies.

*Dropouts*

Dropouts will be recorded with reasons when available. Descriptive analyses will compare baseline characteristics (e.g., age, sex, cognitive scores) between completers and non-completers to assess potential attrition bias. Participant flow will be presented using a CONSORT-style diagram adapted for feasibility trials (Figure 3).

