### 2.6. Timelines and Schedule

After participant selection, an initial in-person session will be held with the participants and their legal guardians. During this session, instructions for starting the study, information on how to use the DiverAcción platform, available communication channels, and data security measures will be provided. Initial data collection (baseline, T0) will also take place during this session.

Training sessions will be conducted over the following six weeks, entirely online and under the remote supervision of the research team’s therapists. Once the twelve sessions are completed, a second in-person data collection session (post-intervention, T1) will be held during the same week the intervention ends.

Finally, a third evaluation (follow-up, T2) will be conducted three months after the intervention ends to assess the maintenance of the effects and long-term adherence. The three-month follow-up interval was chosen based on prior research on executive function interventions in children and adolescents with ADHD, where short- to medium-term maintenance of effects is commonly assessed within a 3–6-month window. This timeframe is considered sufficient to detect initial trends in maintenance or potential decay of intervention benefits while balancing feasibility and participant burden in a feasibility study. Previous studies have reported sustained improvements in working memory, attention, and processing speed at three-month follow-up after cognitive or combined interventions [39,49,50]. Therefore, the three-month interval aligns with established practices and provides meaningful preliminary data on the durability of intervention effects.

Therefore, data collection will take place at three points in time:Baseline (T0): before the start of the intervention.Post-intervention (T1): immediately after the twelve sessions.Follow-up (T2): three months later.

All in-person sessions will be held in a classroom at the local University. The flowchart in Figure 1 shows the timeline of the different phases of the study.

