### 2.7. Sample Size

The planned sample size is 30 children/adolescents. This number is considered adequate for feasibility and usability studies in children and adolescents [25,51], ensuring sufficient variability to identify barriers and facilitators without requiring a formal calculation of statistical power [52]. This study was designed as a pilot trial aimed at assessing the feasibility and acceptability of the intervention. The sample size (n = 30) is considered appropriate for feasibility objectives, as it allows for the evaluation of implementation aspects, adherence, usability, acceptability and participant satisfaction. However, this sample size is insufficient to establish the efficacy of the intervention; Therefore, the findings should be interpreted as preliminary and intended to inform the design of future randomized controlled trials with larger samples.

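### The SUS and TAM means that feed the GO decision leave out children who stop early, and the wording allows adherence to be restricted in the same way

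*Protocol article*

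**What the plan says.** All references are to the protocol article.

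- **Analysis set.** Section 2.9.2, under data completeness: "Primary feasibility analyses will use complete cases". The term is not defined and no feasibility outcome is exempted. The next sentence reads "Sensitivity analyses using multiple imputation may be performed for exploratory clinical outcomes", so imputation does not extend to feasibility measures.
- **Timing of T1.** Section 2.6: "Once the twelve sessions are completed, a second in-person data collection session (post-intervention, T1) will be held during the same week the intervention ends". The list of time points repeats it: "Post-intervention (T1): immediately after the twelve sessions". No assessment is described for a child who stops before the twelfth session.
- **Where the scores come from.** Table 2 schedules TAM, SUS, the design rating, satisfaction and WAI-I at T1 only. It also enters the automated platform metrics, adherence among them, at T1.
- **Adherence.** Section 2.9.2 reports the share of participants who satisfy three criteria, one being at least 80% of scheduled training activities. Section 2.4.9 says the platform also logs tasks left unfinished and tasks never started.
- **Decision rule.** Table 3 sets GO at SUS 68 or more, mean TAM 3.5 or more, adherence 80% or more, retention 80% or more and dropout 20% or less.

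**The concern.** In a feasibility study, a child who stops is part of the result. SUS and TAM are meant to show whether the platform is usable and acceptable, and children who found it neither are among the likeliest to stop before session twelve. If they have no T1 visit, they have no score. A complete-case mean then answers a narrower question: how usable the platform was for those who finished.

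The two timing rules also sit badly together. Adherence accepts 80% of the training, but T1 is tied to all twelve sessions. If sessions are the unit of count, 0.8 × 12 = 9.6, so a child with 10 or 11 sessions meets the training criterion yet has no defined T1 assessment.

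At stake is the progression decision. Table 3 determines whether a definitive trial follows, and two of its eight domains would rest on a selected group. Adherence would be a third if the restrictive reading were adopted.

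**Working it through.** There is no figure of the plan's own to reproduce. Section 2.7 says "The planned sample size is 30 children/adolescents", justified "without requiring a formal calculation of statistical power". The check is denominator arithmetic.

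**Inputs.** N = 30 (section 2.7); thresholds from Table 3; d = number who leave; n = 30 − d completers. Completer means for SUS and TAM are assumptions, because the documents give none. Adherence is taken as a proportion of participants, as section 2.9.2 defines it.

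**Do retention and dropout reveal the problem?** Take d = 6. Dropout is 6/30 = 20% (GO). If the other 24 complete every T1 and T2 assessment, retention is 24/30 = 80% (GO).

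**Adherence under the two denominators.** For each d, take the smallest number of adherent completers that reaches 80% of n, then divide the same number by 30, counting leavers as non-adherent.

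| d | Dropout | Complete cases | All enrolled |
|---|---|---|---|
| 1 | 3.3% | 24/29 = 82.8% (GO) | 24/30 = 80.0% (GO) |
| 2 | 6.7% | 23/28 = 82.1% (GO) | 23/30 = 76.7% (AMEND) |
| 3 | 10.0% | 22/27 = 81.5% (GO) | 22/30 = 73.3% (AMEND) |
| 6 | 20.0% | 20/24 = 83.3% (GO) | 20/30 = 66.7% (AMEND) |
| 8 | 26.7% | 18/22 = 81.8% (GO) | 18/30 = 60.0% (AMEND) |

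One leaver cannot change the verdict; two can. At d = 6 the Wilson 95% intervals are 64% to 93% for 20/24 and 49% to 81% for 20/30. At d = 8 the dropout criterion (26.7%) and retention (at most 22/30 = 73.3%) already read AMEND, so d = 6 is the more telling case.

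If T1 is held only after all twelve sessions and adherence is computed on T1 cases, every such case has done 12 of 12. The training criterion is then met by construction when sessions are the unit.

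**SUS and TAM break-even.** The all-enrolled mean falls below threshold t when the leavers' mean is below (30t − n × completer mean)/d. With d = 6 and n = 24:

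- SUS, completer mean 70: (30 × 68 − 24 × 70)/6 = (2040 − 1680)/6 = 60. For completer means of 72 and 75 the break-even is 52 and 40.
- TAM, completer mean 3.6: (30 × 3.5 − 24 × 3.6)/6 = (105 − 86.4)/6 = 3.1. For completer means of 3.8 and 4.0 it is 2.3 and 1.5.

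A completer mean just above the threshold is therefore fragile. A comfortable one is not.

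**The case against.** A reader might infer that the complete-case rule makes retention and completeness 100% by construction and that every bias runs towards GO. The document does not support either. Retention and completeness are defined over participants in section 2.9.2, and Table 3 gives them and dropout STOP values that could never occur on that reading. The T1 trigger can even lower retention, because a child with no T1 counts as not retained.

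For adherence the defence is strong. The components have fixed denominators (days over six weeks, scheduled activities), the logs exist for children who stop, and a complete-case rule need not remove a child whose data are not missing. The T1 entry in Table 2 may only mark when the log is extracted. Exclusion of leavers is thus a permitted reading, not a certain one.

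On timing, the sentence that ties T1 to the twelve sessions also places it in the week the intervention ends, so a calendar reading is possible. It is not stated, and the list of time points repeats the session-based definition.

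Other safeguards exist. Reasons for dropout are recorded, completers and non-completers are compared at baseline, comments are gathered at the videoconferences in weeks 1 and 3, and adults also complete SUS and TAM. None of these supplies the missing child scores or alters the means compared with 68 and 3.5, and the adults' questionnaires are likewise scheduled only at T1.

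A condensed article may leave visit rules for early stoppers to the full protocol. That explains the silence about an exit assessment. It does not dispose of the complete-case sentence or the T1 definition, which are stated rules.

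**Conclusion.** The point holds for usability and acceptability: as written, the SUS and TAM means come from finishers, and no planned analysis shows what the missing scores could do. For adherence it is a consequential ambiguity. With 20% dropout, which Table 3 still rates GO, the same 20 adherent children give 83.3% or 66.7% depending on the denominator, which is GO or AMEND.

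The adherence contrast assumes that leavers are non-adherent and that Table 3 uses the proportion defined in section 2.9.2. Its adherence row could also be read as a mean percentage. The SUS and TAM break-even values rest on assumed completer means. They show that a verdict can turn, not that it will.

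**What to change.** Four changes, made before any outcome data are seen:

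1. Replace the complete-case sentence. Retention, completeness, adherence and dropout take all enrolled children as denominator; recruitment keeps the eligible children approached. A child who stops counts as non-adherent unless the platform logs show that the criteria were met.
2. Set T1 by calendar, at the end of week 6, and T2 three months later, whatever number of sessions was done.
3. Offer SUS and TAM online at withdrawal.
4. Report how many children answered SUS and TAM, and how each verdict changes under low scores for those who did not.

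The cost is a change of wording and one short online form. Section 2.9.1 already administers self-report through digital tools, and the platform logs usage automatically. The reported figures may be less favourable.
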